## Abstract

**Background:**

Young people with disabilities often lag behind their typically developing peers in the achievement of adult roles, which has been attributed to a lack of opportunities to develop critical life skills. Residential Immersive Life Skills (RILS) programs provide situated learning opportunities to develop life skills alongside peers and away from home in real-world settings. Retrospective research suggests that attending RILS programs is a transformative experience that empowers youth, provides parental hope, and increases service provider expertise. However, prospective, comparative research is needed to determine longer term benefits of these programs on youth life trajectories, in addition to exploring the program features and participant experiences that optimize program success. This protocol describes a 5-year, multi-site prospective study examining the effects of RILS programs for youth with disabilities.

**Methods:**

The study involves RILS programs at three sites in Ontario, Canada. Cohorts of treatment and control groups will receive the study protocol over 3 successive years. Thirty English-speaking participants aged 14–21 years with a child-onset disability and the cognitive capacity to engage in goal setting will be recruited every year for 3 years in the following groups: youth attending a RILS program (Group A); a deferred RILS control group of youth (Group B); a control group of youth attending a non-residential life skills program (Group C); and a control group matched on age, diagnoses, and cognitive capacity not receiving any life skills intervention (Group D). All participants will complete measures of self-determination and self-efficacy at four time points. Program opportunities and experiences will also be assessed in-the-moment at the RILS programs. Qualitative interviews pre-program and at 3- and 12-months post-program will be undertaken with a sub-sample of youth and parents to explore their expectations and experiences.

**Discussion:**

This study will address key gaps in the literature pertaining to the long-term impact of RILS programs and the role of immersive environments in shaping youth outcomes and experiences. Our research program aims to uncover transferable processes and essential features by which RILS programs have their effects on attitudes, cognitions, and behaviour.

**Trial registration:**

The trial registration number on clinicaltrials.gov is NCT02753452 (retrospectively registered 26 April 2016).

Trial sponsor: Holland Bloorview Kids Rehabilitation Hospital.

## Background

In Canada, between 3.5 and 7.7 % of children under 19 years of age are estimated to have a chronic health condition that results in disability or activity limitations [1, 2]. Despite having the same life aspirations as their typically developing peers [3, 4], they often lag behind them in achieving adult roles with respect to independent living, personal relationships, education, and employment [5–7]. A combination of physical, cognitive, and social restrictions result in a lack of opportunities and experiences needed by youth with disabilities to acquire the life skills vital for the achievement of adult roles [8]. This protocol outlines a 5-year multi-site prospective cohort study that will examine the effects of residential immersive life skills (RILS) programs for youth with disabilities. The study will contribute to our understanding of how these programs provide youth with the opportunities and experiences needed to attain successful life outcomes. The protocol adheres to the SPIRIT guidelines for reporting of clinical trial protocols (http://www.equator-network.org/reporting-guidelines/spirit-2013-statement-defining-standard-protocol-items-for-clinical-trials/).

Life skills are adaptive, positive behaviours that enable an individual to meet the challenges and demands of everyday life effectively [9]. Two key life skills targeted by life skills programs are self-determination and self-efficacy [10, 11]. Self-determination refers to the ability to make choices and have control over one’s life [12]. A strong sense of self-determination is associated with improved life outcomes among youth with disabilities [13, 14]. Self-efficacy-a central component of self-determination theory-is the feeling of being capable of taking action and coping with challenges [15]. When youth lack opportunities to tackle and succeed in mastering day to day tasks, this can lead to an underdeveloped sense of self-efficacy, which has been associated with poorer psychosocial outcomes [16, 17]. Conversely, mastering developmentally appropriate skills has been found to lead to greater psychological wellness in youth [18]. Young people with disabilities may be prevented from exploring independently or testing their strengths by parents worried for their safety or about the impact failure may have on them [19]. Unfortunately, such restrictions may result in youth having lowered expectations of themselves and performing below their capabilities [20]. Program models that combine the challenge of real-world settings with opportunities for exerting control may therefore be particularly effective for the development of youth self-determination and self-efficacy [21].

Life skills programs have targeted many vulnerable populations to support the development of critical skills during adolescence and young adulthood. They typically include a combination of structured group education sessions, coaching, and peer mentorship [22]. Through teaching concrete tasks such as budgeting and laundry that will equip young people with the skills needed for independent living, the programs aim to develop higher order skills such as self-efficacy and self-determination.

### Residential immersive life skills (RILS) programs

RILS programs are a unique type of life skills program for youth with disabilities and provide opportunities for learning with peers in a university or college residence, for periods between one and three weeks. RILS programs use flexible, multi-faceted approaches to provide experiences in choice-making, facilitated goal-setting, trial and error learning, and risk taking [22]. RILS programs appear to provide opportunities for ‘situated learning’, a powerful educational approach where learning occurs within the environments where the skills will be needed [23], which increases their potential to provide sustainable gains. Expert service providers report intentionally creating a safe, supportive, and engaging environment at RILS programs and tailoring learning strategies to the needs of the youth [24]. Non-intrusive strategies are common, such as allowing youth to ‘fail safely’, thus experiencing the consequences of their decisions in a supported environment. This can result in feelings of empowerment and self-determination [24].

The residential nature of RILS programs offers repeated opportunities to master skills and also allows youth to learn skills as part of their everyday life, termed ‘experiential learning’ [25]. RILS programs also facilitate interactions with peers with disabilities, offering intense learning and social experiences that go beyond skill development [26]. For some participants, this is one of their first opportunities to engage with others with disabilities, which may lead to greater understanding of their identity [27]. RILS programs often result in profound changes in young people and have been described as a ‘turning point’ in their transition to adulthood [28]. Secondary benefits may also arise: Service providers report their own clinical practice to be positively impacted by spending extended time with the youth and witnessing their daily reality, while parents often experience a transformation in their hopes and expectations for their child’s future [28].

A pilot study by our team previously used a range of measures to capture the environmental opportunities, in-the-moment experiences, and intervention strategies used in an established RILS program [29]. Findings demonstrated high program fidelity i.e., it was delivered and experienced as intended. There was also evidence that the RILS program provided a facilitative environment enabling youth to develop autonomy, self-determination, and self-efficacy. This pilot work therefore informed the design of the protocol described here and confirmed the suitability of the selected measures, which will be able to examine program features and experiences that may contribute to youth outcomes over time.

### Research gap

Although the findings to date are promising with regard to the impact of RILS programs, the unique immersive nature of RILS programs, which may enhance or accelerate the development of life skills, has not been examined. Furthermore, research has focused on short-term changes related to self-determination, self-concept, and preparedness for life [22, 30]. There is a lack of research on the sustainability and/or consolidation of skills acquired in the programs, and the emergence of higher-order life skills after additional practice and reflection. Critically, the processes and essential features by which RILS programs have their effects on attitudes, cognitions, and behaviour require further explication, including the role of peer interactions. Finally, research has largely been retrospective in nature (e.g., [24, 27, 28]).

### Objectives

Our objectives are to understand the ways in which RILS programs lead to changes in youth outcomes and to determine the sustainability of these changes. In addition, we will identify the processes and intervention strategies integrated into program delivery, and explore the experiences of participants and their parents before, during, and after the program.

### Aims

Our specific study aims are as follows:To examine the nature of the opportunities provided by RILS programs for particular types of youth experiences, and the extent to which service providers use specific learning strategies to promote the acquisition of core skills, knowledge, and behaviours.To explore the subjective experiences of youth and parents before, during, and after the program.To assess change and/or maintenance in outcomes, namely youth development of higher-order life skills (self-efficacy and self-determination) up to 1 year post-program, when compared to three groups of matched youth.

## Methods/design

### Research design

The study uses a mixed-methods approach to assess the complex opportunities, experiences, and outcomes of RILS programs [31]. This 5-year multi-site prospective study will employ a time series with non-equivalent control group (TSNECG) design, which will control for many threats to validity and allow reasonable attribution of the effects to the RILS program intervention [32]. Specifically, the TSNECG design will allow us to determine whether exposure to RILS programs has an effect on higher-order life skills compared with the three comparison groups, assessed from pre-intervention to immediately post-intervention, and at 3- and 12-month follow-up assessments.

### Settings and intervention

Three core organizations in the province of Ontario, Canada, deliver well-established RILS programs. Program coordinators from these three organizations have collaborated for over 10 years to develop the programs and thus they share common goals and a common philosophy.

The programs run once per year over the summer. Each is delivered by a team of service providers, including occupational and physical therapists, therapeutic recreation specialists, life skills facilitators, nurses, social workers, and personal attendants. All programs take place in a university or college residence for periods of one to three weeks.

Although self-determination theory was not explicitly used in the initial design of the RILS programs, repeated opportunities for youth to make decisions and to practice daily tasks (e.g., budgeting, laundry, directing personal care, cooking, navigation, meal planning) aim to promote the development of self-determination and self-efficacy.

To participate in the programs, youth must have a child-onset disability, the cognitive capacity to set goals, and must not have behavioural issues that would interfere with their ability to participate in a group learning experience. Youth with mild cognitive impairments, as assessed by clinicians, are eligible to participate. The age range for participation in the programs is 14 to 21 years. Past participants in the three RILS programs have had diagnoses of cerebral palsy (50 %), spina bifida (15 %), acquired brain injury (5 %), communication disorders (5 %), as well as other conditions (25 %).

### Research participants

Participants will be enrolled in four groups, with new participants recruited each year for three successive years. For practical and ethical reasons, we cannot randomly assign youth to treatment and control conditions.

Group A will consist of participants drawn from the youth enrolled in the three RILS programs. All youth will be English speaking, as this is the language of instruction of the RILS programs. In addition to meeting the eligibility requirements for program participation, as described above, youth who wish to participate in the research project will be screened separately by the research coordinator for their capacity to provide informed consent to participate in the study. Parents of youth in Group A must be English speaking to participate in interviews.

Group B will consist of youth who apply and are eligible to participate in one of the RILS programs but who are placed on a ‘deferred’ list to attend the program in the following year. This can be for a number of reasons, including numbers of places available and demand, extent of care needs, and youth availability. This group is intended to control for the motivation participants have for taking part in a RILS program.

Group C will consist of youth taking part in a group life skills program that is not residential. Several life skills programs at treatment centres in Ontario run over multiple days/weeks and employ a group format without being residential. This group will allow us to examine the relative effect of the immersive component of the RILS programs.

Group D, the control group, will consist of clients who are not participating in any group life skills program but are registered with one of six Ontario children’s treatment centres (the three core centres offering RILS programs, plus three additional collaborating centres).

Youth in the three comparison groups (Groups B, C, and D) must meet the eligibility criteria for the RILS programs, to ensure comparability with Group A. They will be matched to the RILS group in terms of age, gender, and diagnosis.

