### Instruments

#### Quantitative data

We will collect baseline demographic information on all participants, including youth age, disability, mobility, health status, ethnic or cultural background, where the youth is living and with whom, and the size of their home community.

At baseline, and at three follow-up time points, all youth will complete measures of self-determination and self-efficacy using an online survey. The Arc’s Self-Determination Scale (SDS) adolescent version includes four subscales (autonomy, self-realization, empowerment, and self-regulation) and provides an overall score of self-determination [33]. Self-determination percentile scores can be generated based on norms from a population of US special education students (ages 14 to 22 y) with a wide range of disabilities. Internal consistency is high (Cronbach’s alpha = 0.90) and criterion-related validity is adequate (*r* = 0.25 to 0.5) [34]. The youth will complete all of the subscales except the self-regulation subscale, which uses a story-writing format requiring subjective scoring and can be sensitive to geographic, cultural, and socioeconomic differences among participants [33]. The General Self-efficacy Scale (GSE) is a 10-item self-administered tool with a 4-point Likert response scale [35] and has been used in numerous research studies to examine perceived self-efficacy. It is valid and reliable with internal consistencies ranging from 0.75 to 0.91.

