To capture in-the-moment experiences during the program, youth will complete the Self-Reported Experiences of Activity Settings (SEAS) measure [38] following selected program activities. The SEAS is a 22-item, youth-completed measure of situation-specific experiences, assessing Personal Growth, Psychological Engagement, Social Belonging, Meaningful Interactions, and Choice & Control. Internal consistency of the SEAS is good to excellent (Cronbach’s alpha from 0.71 to 0.88), with moderate test–retest reliability (mean scale intra-class correlation coefficient = 0.68) [38]. The SEAS is available at https://flintbox.com/public/project/25724/

The schedule of data collection for the study is shown below, in Table 1. All of the measures have been piloted in a RILS program [29]. This pilot work indicated that RILS program features and youth experiences can be reliably and meaningfully assessed *while they are occurring,* and the convergence between the measures demonstrated that youth experienced the program as service providers intended. The measures employed in this current study therefore have demonstrated high feasibility [29].

**Table 1 Tab1:** Schedule of research activities by group

Research Activities	Baseline	During Life Skills Programs	Follow-up		
			1 week post-program	3 months post-program	12 months post-program
Enrollment:					
Eligibility Screen	A, B, C, D				
Informed Consent	A, B, C, D				
Demographic Form	A, B, C, D				
Intervention:					
Life Skills Programming		A, C			
Life Skills Program Assessments:					
Service Providers’ Strategies-Checklist (SPS-C)		A			
Measure of Environmental Qualities of Activity Settings (MEQAS)		A			
Participant Assessments:					
Self-Reported Experiences of Activity Settings (SEAS)		A			
Arcs’s Self-Determination Scale	A, B, C, D		A, B, C, D	A, B, C, D	A, B, C, D
General Self-Efficacy Scale (GSE)	A, B, C, D		A, B, C, D	A, B, C, D	A, B, C, D
Qualitative Interview	A, C			A, C	A, C

**Group A**: Participants drawn from the youth enrolled in Residential Immersive Life Skills programs*.*
**Group B**: Participants drawn from the youth deferred from Residential Immersive Life Skills programs*.*
**Group C**: Participants drawn from youth enrolled in non-residential Life Skills programs*.*
**Group D**: Participants not participating in any group life skills program

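### On the planned schedule, many or most of Group B are due to be in, or just out of, their own RILS program at the 12-month survey, so the 12-month A-versus-B contrast is likely contaminated

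*Protocol article*

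**What the plan says.** Five parts of the protocol article bear on this.

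- **Who Group B is** (Research participants): eligible applicants placed on a deferred "list to attend the program in the following year". The group's stated purpose is to control for motivation to attend. The reasons given for deferral are limited places, care needs and availability.
- **When programs run** (Settings and intervention): "The programs run once per year over the summer". On length: "All programs take place in a university or college residence for periods of one to three weeks".
- **When outcomes are measured** (Research design; Instruments, Quantitative data): "At baseline, and at three follow-up time points, all youth will complete measures of self-determination and self-efficacy using an online survey". The contrasts are "assessed from pre-intervention to immediately post-intervention, and at 3- and 12-month follow-up assessments". Table 1 lists Groups A, B, C and D for both outcome scales at every follow-up, including "12 months post-program", and lists life skills programming for A and C only.
- **What is claimed** (Aims): change or maintenance "up to 1 year post-program, when compared to three groups of matched youth".
- **How it is analysed** (Quantitative analysis): A is tested against one comparison group at a time, in a baseline-adjusted repeated measures ANCOVA with three longitudinal points. The 12-month survey is one of the three.

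The article does not say what post-program is counted from for Group B, which has no program in its first year. The Limitations section deals with withdrawal and loss to follow-up, not with comparison youth receiving the intervention.

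**The concern.** The deferral lasts one program cycle, and one cycle is about 12 months, which is also the length of follow-up. Group B therefore stops being an unexposed comparator at about the time of its last survey. A contrast at that point no longer asks whether RILS effects last a year. It compares youth a year after RILS with a group that is partly or wholly fresh from it.

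The study is not randomised, and Group B is the only comparator assigned to handle motivation to attend. If its 12-month value is contaminated, an effect that Group A has fully kept could look like decay, and the group-by-time pattern would mislead in the same direction. An unexposed 12-month value cannot be recovered once a youth has attended.

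**Working it through.** **1. The plan's own sample size.** Inputs (Statistical power): d = 0.50, power 0.80, alpha 0.05 one-tailed.

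n per group = 2 × (1.645 + 0.842)² / 0.50² = 49.5, rounded up to 50. This reproduces the stated 50. Attrition of one-third gives 90 × 2/3 = 60 per group, also as stated. The 60 is used below.

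**2. Timing.** Let day 0 be the end of Group A's program, and suppose next year's run falls in the same calendar week, so that it ends on day 364. With program length L days it starts on day 364 − L.

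| Next year's run | 1-week program (L = 7) | 3-week program (L = 21) |
|---|---|---|
| Same week | days 357–364: finished by day 365 | days 343–364: finished by day 365 |
| 7 days later | days 364–371: in program on day 365 | days 350–371: in program on day 365 |
| 14 days later | days 371–378: not yet started | days 357–378: in program on day 365 |

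Group B is unexposed on day 365 only if 364 − L + shift > 365, that is, if the run moves later by more than L + 1 days, or if the survey is taken early. Day 335, for example, precedes the start in all six cells.

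**3. Size at 12 months.** Two quantities are not in the article and are assumptions here:

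- r = the share of Group A's 0.50 SD effect retained at 12 months;
- f = the share of Group B already exposed, each assumed to have gained a full, fresh 0.50 SD.

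Expected contrast = 0.50 × (r − f).

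Power for A > B = Φ(contrast / √(2/60) − 1.645), with √(2/60) = 0.183. This is the simple two-mean comparison behind the plan's sample size, without gain from baseline adjustment.

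With full retention (r = 1):

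| f | Contrast (SD) | Power |
|---|---|---|
| 0 | 0.500 | 0.86 |
| 0.25 | 0.375 | 0.66 |
| 0.50 | 0.250 | 0.39 |
| 0.75 | 0.125 | 0.17 |
| 1 | 0 | 0.05 |

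With partial retention and all of B exposed (f = 1), r = 0.75 gives −0.125. With r = 0.50 the contrast is −0.25, and the chance that the observed difference favours B is Φ(0.25 / 0.183) = 0.92.

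**4. Interpretation.** The contrast depends only on r − f. A value of 0.25 SD arises from full retention with half of B exposed (1 − 0.50), and equally from half retention with none exposed (0.50 − 0). Without attendance data the 12-month A-versus-B result cannot separate maintenance from loss of effect, and that distinction is what the aim asks about.

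**The case against.** **Certainty.** The article gives no program dates by site, no survey window and no attendance rate for deferred youth. A shift of days to weeks decides whether a youth is surveyed before, during or after the program. The reasons for deferral may recur, so some of Group B may not attend the following summer. Table 1 is also compatible with all of Group B's surveys falling before its own program. Survey windows are a detail that a condensed article may leave to the full protocol. This stands: the text supports saying that Group B is scheduled for exposure at about that time, not that every member will have been exposed. It does not remove the problem. The article itself fixes the deferral, the annual cycle, the 12-month survey and the model that uses it, and these collide on the nominal schedule. Counting Group B's visits from its own program would not help, since all its follow-ups would then come after exposure.

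**Direction and size.** A reader might infer that the contrast will reverse and the overall effect be nearly halved. If Group A's effects are assumed to be 0.50, 0.40 and 0.30 SD and all of B gains 0.50, the 12-month contrast is 0.30 − 0.50 = −0.20. The three-visit mean is then (0.50 + 0.40 − 0.20)/3 = 0.23 instead of 0.40, a fall of 42%. The documents do not support this as a prediction. No passage states that effects decay, and the Research gap section raises consolidation and later emergence of skills. With assumed effects of 0.50, 0.60 and 0.70, the 12-month contrast is 0.70 − 0.50 = +0.20 and the mean is (0.50 + 0.60 + 0.20)/3 = 0.43 instead of 0.60: attenuated, not reversed. Full exposure is assumed in both cases, and the article does not name the three-visit mean as its test.

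**Scope.** One contrast of three is affected directly, at one follow-up of three. This also stands. The aim still has two other 12-month comparators, though neither is assigned to control for motivation.

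**Conclusion.** The concern holds in a limited form. On the protocol's own schedule, many or most Group B youth are due to be attending or to have just finished RILS at the 12-month survey, and nothing in the article deals with this. The 12-month A-versus-B contrast, and any A-versus-B effect or group-by-time test that includes it, is likely biased in Group B's favour.

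The amount is 0.50 × f SD, if exposed Group B youth gain the planned effect in full. With full retention in A, power falls from 0.86 to between 0.66 and 0.05 as f goes from 0.25 to 1. Reversal of the expected sign requires r < f, and the documents give neither figure, so reversal is a possibility and not a finding.

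**What to change.** 1. State in Table 1 what Group B's follow-up visits are counted from.
2. Choose one of two routes:
   - take Group B's last survey before its own program starts, at about 11 months and labelled as such. Tie it to that youth's program start date, because a fixed day can still fall inside a run that is held earlier;
   - limit A versus B to the 1-week and 3-month points, with A versus C and A versus D carrying the 12-month claim.
3. Record the dates of any RILS attendance before the 12-month survey.
4. Do not use Group B's data from after attendance as control data. Simply keeping the non-attenders is not a substitute, since they would be a selected subset.

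The cost is a table footnote, a changed date for an online survey and one added question. The downside is either a slightly earlier last control point for Group B, or no motivation-matched comparator at 12 months. The change has to be made before Group B attends.

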In addition, a number of measures will be collected on-site during the RILS programs for Group A participants. Trained observers will complete the 48-item Measure of Environmental Qualities of Activity Settings (MEQAS-48) to capture program opportunities. Validated with life skills program activity settings, the MEQAS is a reliable and valid measure of aesthetic, physical, social, and opportunity-related qualities of leisure activity settings for youth with or without disabilities [36]. Observers use a 7-point scale to rate the extent to which the observed activity setting includes various features. The MEQAS has a sound factor structure and preliminary evidence of internal consistency, inter-rater reliability, and test-retest reliability. Cronbach’s alpha for the scales (Comfortable Place-related Qualities, Pleasant Physical Environment, Opportunities for Choice, Opportunities for Privacy/Relaxation, Opportunities to Interact with Peers, Opportunities for Personal Growth, Opportunities for Physical Activities, Opportunities for Cooperative Group Activity, and Opportunities to Interact with Adults) range from 0.82 to 0.97 [36]. Inter-rater reliability and test-retest reliability were established on a previous version, the MEQAS-32, with inter-rater reliability (ICC) ranging from 0.60 to 0.93 and test-retest reliability ranging from 0.70 to 0.90. The MEQAS-48 is available at https://flintbox.com/public/project/25723/

Trained observers will also complete the Service Providers’ Strategies-Checklist (SPS-C), a 24-item checklist that captures service providers’ actual use of intervention strategies in life skills programs, including teaching/learning techniques, handling/physical interventions, socially-mediated strategies, cognitive strategies, and non-intrusive strategies. Items were constructed based on service providers’ descriptions of their use of strategies in a qualitative study of RILS service providers and an existing checklist of intervention strategies for school-based therapy [37]. Content validity of the SPS-C was established through review by RILS service providers and clinicians on the research team, and it has a high inter-rater agreement (96 %). The SPS-C will allow us to characterise and compare the strategies used by service providers across the RILS programs. The SPS-C is available at http://flintbox.com/public/project/27313/

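### Group C is said to show the effect of the immersive component, but the design compares whole programs and does not separate residence from the rest of the package

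*Protocol article*

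**What the plan says.** Research participants gives the purpose of Group C in one sentence: "This group will allow us to examine the relative effect of the immersive component of the RILS programs". It describes the comparator programs as follows: "Several life skills programs at treatment centres in Ontario run over multiple days/weeks and employ a group format without being residential". The same section states that "we cannot randomly assign youth to treatment and control conditions". Comparison youth must meet the RILS eligibility criteria and are matched to Group A on age, gender and diagnosis.

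Settings and intervention describes the RILS programs more fully. On setting and length: "All programs take place in a university or college residence for periods of one to three weeks". On their common origin: "Program coordinators from these three organizations have collaborated for over 10 years to develop the programs". A multidisciplinary staff is listed.

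For process data, the Quantitative data section says that "a number of measures will be collected on-site during the RILS programs for Group A participants". Table 1 marks MEQAS, SPS-C and SEAS for Group A alone. Qualitative interviews are scheduled for Groups A and C before the program and at 3 and 12 months, with 15 youth in each group.

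Quantitative analysis tests Group A against one comparison group at a time by repeated measures ANCOVA. Baseline score is the only covariate named. The multilevel model concerns the three program sites.

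**The concern.** Immersion is one feature of a RILS program. To read an A-minus-C difference as its effect, the two kinds of program would have to be alike in other respects that affect self-determination and self-efficacy, or those respects would have to be measured and taken into account. The article provides for neither.

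This matters because the immersion question is the only purpose stated for Group C, a group of 90 recruited youth, and because the Research gap section says that the immersive nature of RILS has not been examined. The Discussion glosses immersive environments as the opportunities provided and the experiences youth have. MEQAS is there to capture opportunities and SEAS to capture experiences, so the construct is quantified on one side only of the contrast meant to test it. Followed as written, the plan would report a whole-program difference as an immersion effect.

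**Working it through.** **Side by side.** What the article states for each group, and whether design or analysis deals with it:

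| Feature | Group A | Group C | Held equal, matched or adjusted? |
|---|---|---|---|
| Residence | Yes | No | The feature of interest |
| Length | One to three weeks | Days or weeks, no limits given | Not stated |
| Contact hours | Not given | Not given | Not stated |
| Content | Everyday tasks and decision making | Not described | Not stated |
| Staffing | Multidisciplinary team | Not described | Not stated |
| Youth | Enrolled in RILS | Enrolled elsewhere, RILS-eligible | Matched on age, gender, diagnosis; baseline score as covariate; not randomised |
| MEQAS, SPS-C, SEAS | Yes | No | Not comparable |
| Interviews | 15 youth (and 10 parents) | 15 youth | Compared qualitatively |

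**What the contrast estimates.** Write the expected A-minus-C difference as

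Δ = immersion + other program features + residual selection.

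The outcome data give one number, Δ. Matching and the baseline covariate act on the last term only, and only in part. Nothing stated acts on the second term.

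**The plan's own figure.** Statistical power gives 50 per group for d = 0.50, power 0.80, α = 0.05 one-tailed. By the normal approximation, n = 2(1.645 + 0.842)² / 0.50² = 2 × 6.185 / 0.25 = 49.5, so 50. The t test gives 50.2. Attrition: 90 × (1 − 1/3) = 60. Both figures reproduce. With 60 per group, one-tailed power for d = 0.50 is 0.86. That power is for Δ as a whole.

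**Illustration.** The shares and biases below are assumptions; the documents give none. The test is a two-sample one-tailed t test with 60 per group, which is simpler than the planned ANCOVA.

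- Suppose part of a total d = 0.50 is due to immersion. The power that 60 per group would have for a difference of that size alone is:
  - 75 %: d = 0.375, power 0.65
  - 50 %: d = 0.25, power 0.39
  - 25 %: d = 0.125, power 0.17
- Suppose immersion has no effect, and other program or selection differences produce d = b. The probability of a significant A-versus-C result is:
  - b = 0.1: 0.14
  - b = 0.2: 0.29
  - b = 0.3: 0.50

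  With b = 0 it would be 0.05.

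A larger sample would raise these last probabilities, so sample size does not resolve the attribution.

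**The case against.** Five points can be made for the plan.

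- **The wording is modest.** The article speaks of examining a relative effect, calls its design one with non-equivalent controls, and under Research design directs attribution to the RILS intervention as a whole. The third aim states no estimand that isolates immersion. This stands, and it is why rewording is enough. The Group C sentence still names the component.
- **Group C is not without process information.** Fifteen of its youth are interviewed, including about program activities and experiences, and Qualitative analysis plans a comparison of RILS with non-residential programs. This stands, so it would be wrong to say that no process information is collected in Group C. But the account of the program is given 3 months afterwards by a subsample, and it cannot adjust the outcome contrast. Qualitative analysis also mentions debrief interviews and field notes from during the program without naming the group; Table 1 schedules no Group C assessment at that time.
- **More exposure is partly what residence is.** The Background says that living in gives repeated practice as part of everyday life. Extra hours are therefore not a clean rival to immersion. This stands. Content, staffing and selection are a different matter.
- **The article is condensed.** Descriptions of the Group C programs may sit in a fuller protocol, so their absence here is not itself a fault. The point rests on what is stated: the attribution, the matching variables, the covariate and the A-only schedule.
- **Giving SEAS to Group C is not trivial.** It is completed after selected activities, so it would need on-site administration, and it would not by itself identify an immersion effect. This stands.

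**Conclusion.** The point holds as one of attribution. A versus C is a legitimate comparison of RILS programs as delivered with existing non-residential group programs. It does not identify the effect of immersion alone, and a significant result should not be reported as such. The size of the possible misattribution cannot be derived from the documents. The probabilities of 0.14 to 0.50 rest on assumed biases of d = 0.1 to 0.3 and a simple t test.

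Two stronger readings are tempting and are not supported:

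- A reader might infer that the two kinds of program do differ in length, content, staff and centre. The documents show only that these are not stated to be equalised or adjusted for. The lengths may overlap, Group C content and staff are not described, and the comparator sites are identified only as Ontario treatment centres, which does not exclude the core RILS organizations.
- A reader might infer that RILS delivers many times the contact hours, so that dose is inseparable from group. Contact hours are given for neither group, so any ratio would follow from the hours chosen for the calculation.

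**What to change.** 1. Reword the purpose of Group C: the A-versus-C contrast estimates the effect of RILS programs as delivered relative to existing non-residential group life skills programs. State that a difference will not be attributed to immersion alone.
2. Have the coordinator of each Group C program complete one form giving days, contact hours, content and staffing, so that the programs can be described beside RILS. If a fuller protocol already collects this, refer to it.
3. Say that the planned interviews in Groups A and C will be used to interpret any difference, not to adjust it.
4. Treat SEAS in Group C as optional. It would allow reported experiences to be compared, at the price of on-site administration.

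The cost of steps 1 to 3 is a slightly narrower claim and one short form per program. Sample size, outcome measures and visits do not change.
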